## Abstract

**Background:**

Age-related hearing loss (ARHL) signifies the bilateral, symmetrical, sensorineural hearing loss that commonly occurs in elderly individuals. Several studies have suggested a higher risk of dementia among patients diagnosed with ARHL. Although the precise causal association between ARHL and cognitive decline remains unclear, ARHL has been recognized as one of the most significant factors that can be modified to reduce the risk of developing dementia potentially. Mild cognitive impairment (MCI) typically serves as the initial stage in the transition from normal cognitive function to dementia. Consequently, the objective of our randomized controlled trial (RCT) is to further investigate whether the use of hearing aids can enhance cognitive function in older adults diagnosed with ARHL and MCI.

**Methods and design:**

This study is a parallel-arm, randomized controlled trial conducted at multiple centers in Shanghai, China. We aim to enlist a total of 688 older adults (age ≥ 60) diagnosed with moderate-to-severe ARHL and MCI from our four research centers. Participants will be assigned randomly to either the hearing aid fitting group or the health education group using block randomization with varying block sizes. Audiometry, cognitive function assessments, and other relevant data will be collected at baseline, as well as at 6, 12, and 24 months post-intervention by audiologists and trained researchers. The primary outcome of our study is the rate of progression to dementia among the two groups of participants. Additionally, various evaluations will be conducted to measure hearing improvement and changes in cognitive function. Apart from the final study results, we also plan to conduct an interim analysis using data from 12-month follow-up.

**Discussion:**

In recent years, there has been a notable lack of randomized controlled trials (RCTs) investigating the possible causal relationship between hearing fitting and the improvement of cognitive function. Our findings may demonstrate that hearing rehabilitation can be a valuable tool in managing ARHL and preventing cognitive decline, which will contribute to the development of a comprehensive framework for the prevention and control of cognitive decline.

**Trial registration:**

Chinese Clinical Trial Registry chictr.org.cn ChiCTR2000036139. Registered on 21 August 2020.

**Supplementary Information:**

The online version contains supplementary material available at 10.1186/s13063-023-07813-z.

## Background

Age-related hearing loss, also known as presbycusis, is a complex syndrome caused by the cumulative effects of aging on the auditory system, characterized by age-related, progressive, bilaterally symmetrical, and sensorineural hearing loss, which usually occurs at high frequencies in older adults firstly [1]. According to the Global Burden of Disease (GBD) Study in 2019, hearing loss has been the third leading cause of global years lived with disabilities among people aged 50 to 69, which became the primary cause among individuals aged 70 and above [2]. And through the data analysis and calculation, ARHL patients have increased from 751 million in 1999 to 1457 million in 2019, accounting for the most percentage of people with hearing loss [3]. The mechanism of ARHL is not clear at present [4], which considered to be a multi-factorial illness with potential risk factors including aging [5], sex [6], environment (noise exposure [7, 8], ototoxic drugs [9]), lifestyle (smoking [10], drinking [11]), comorbidities (diabetes [10, 11]), and genetic predisposition [1, 7, 12, 13].

ARHL induces a huge financial burden, which brings additional outlays of 1 trillion dollars a year [14]. However, there are no effective medicines or surgeries for ARHL until now, while the common intervention is wearing hearing aids [15]. Worse still, in the USA, the hearing aid intervention rate for individuals aged 50 and older was 14.2%, and the rate for individuals aged 65 and older was 6.5% in China [16, 17].

It has been recognized for decades that older adults with hearing loss had a higher risk of dementia [18, 19], in which cognitive decline interferes with the independent daily life of patients in memory, language, problem-solving, and other cognitive kills [20, 21]. Some hypotheses such as the cognitive load hypothesis, common cause hypothesis, and cascade hypothesis suggest the possible relationship between hearing loss and cognitive decline [22]. In recent years, researchers have found that hearing loss is an independent risk factor for accelerating the process of cognitive decline through cohort studies [23–26]. And the Lancet Commissions in 2020 pointed out that hearing loss is the first risk factor which can be preventable for Alzheimer’s disease, which population attributable fraction (PAF) accounted for about 8% of all of the 40% modifiable factors [27].

Nonetheless, the causality between ARHL and cognitive decline is not clear now [28]. According to a recent meta-analysis, the use of hearing aids may be linked to long-term cognitive benefits for older adults [29]. Mosnier compared the cognitive function between profoundly deaf older adults with or without cochlear implantation fitting and found that it was beneficial to the improvement of cognitive function [30]. Zhu found that patients aged 40–69 who have hearing loss without hearing intervention are at a heightened risk of developing all-cause dementia (HR 1.42 [95%CI 1.28–1.57]), while those with hearing loss who use hearing AIDS are not at an increased risk (HR 1.04 [0.98–1.10]) by using data from the UK Biobank [31]. However, in an observational study of 666 community-dwelling older adults with hearing impairment, there were no significant differences between hearing aid users and non-users in cognitive function, social engagement, or mental health outcomes during follow-up interval [32]. Another 6-month follow-up study found that hearing aids did not result in significant improvement in cognitive function among individuals with cognitive impairment and dementia [33]. Therefore, despite the challenges in studying the long-term cognitive effects of hearing intervention, we still need further studies, especially randomized controlled trials like the “ACHIEVE” project initiated by Frank Lin [34], to assess the potential benefits of hearing intervention on cognitive function.

MCI, occurring in the early process of cognitive development from normal to dementia, usually refers to a cognitive disorder which is significantly more severe than cognitive decline in normal aging, while patients retain most of the ability to perform independent activities of daily living [21, 35]. Its prevalence in individuals aged over 60 is reported to be 15.8% [36]. Patients with MCI will have a higher risk of dementia, and even if they return to normal cognition, the risk of subsequent cognitive deterioration is still higher than that of normal people who have never had MCI [37]. Many clinical researchers devote to delay the development of dementia in the pre-clinical stage, which makes MCI become the research hotspot in the dementia field [38, 39].

Since we pay more attention to their connection, the hearing intervention has been considered to be a potential therapy for cognitive decline [19]. Considering the few compelling evidence regarding the extent to which hearing aids play a role in cognition improvement among elders with moderate-to-severe ARHL and MCI, we designed this multicenter, randomized, controlled trial with two parallel groups. The CHOICE project, meaning Chinese Hearing Solution for Improvement of Cognitive in Elders conducted by Shanghai Ninth People’s Hospital, intends to provide the fundamental therapeutic strategy for ARHL management using hearing aids by establishing a cohort of ARHL patients (CHOICE-Cohort) and perform an RCT study (CHOICE-RCT).

## Methods/design

### Study design and settings

This multicenter, parallel-arm randomized controlled trial (RCT) study will be conducted by four tertiary referral clinics (Hospital of the Shanghai Jiao Tong University School of Medicine, China): Ninth People’s Hospital, Sixth People’s Hospital, Ruijin Hospital, and Mental Health Center. The study protocol is drafted following the Standard Protocol Items Recommendations for Interventional Trials (SPIRIT) statement (see additional file 1 for the SPIRIT 2013 Checklist) [40].

Upon recruitment and screening, eligible participants will be randomly assigned to either the hearing aid fitting group or the health education group in a 1:1 ratio. These participants will then receive different interventions and undergo evaluations throughout the entire duration of the trial (see Fig. 1 for a flowchart of the study).

**Fig. 1 Fig1:**
[figure not shown]
Flowchart for the study

Baseline data will be collected at the start of the trial, followed by follow-up assessments at 6, 12, and 24 months after the interventions. These assessments will evaluate the primary outcome, which is the percentage of participants who develop dementia. Secondary outcomes, such as auditory and cognitive function evaluations, will also be measured in both groups.

By following this study design, we aim to compare the effectiveness of hearing aid fitting versus health education interventions in preventing the development of dementia and improving auditory and cognitive function. The participation of multiple centers will enhance the generalizability and robustness of our findings.

### Participants and recruitments

The study will include a diverse population, consisting of individuals seeking assistance for age-related hearing loss (ARHL) at the outpatient clinics of our study centers, those who have been informed about the study through online advertisements, and participants who are already enrolled in the cohort study of the CHOICE project. Since our investigation focuses on the development of dementia, which predominantly occurs in the late stages of life, we will specifically consider individuals who are aged 60 or older in order to ensure the external validity of our findings.

Upon providing signed informed consent, participants will be required to complete a questionnaire that covers their basic information, which is necessary for the research. Additionally, participants will undergo auditory tests and evaluations of cognitive function to fulfill the criteria established for the RCT study.

#### Inclusion criteria

Age ≥ 60Postlingual hearing lossReceived education for at least 6 yearsSensorineural hearing loss35 ≤ PTA (pure tone average at 0.5, 1, 2, 4 kHz) < 80 dB HLMini-mental State Examination ≤ 26Geriatric Depression Scale ≤ 10Activity of Daily Living Scale ≤ 17

#### Exclusion criteria

Used hearing aids within a yearInability to complete cognitive assessmentsConductive hearing lossUnwilling to wear hearing aids dailyHad neurosyphilis or hypothyroidism

### Randomization

Considering that the subjects in our experiment will be aware of whether they have received the hearing aid fitting, we will not be utilizing the double-blind method. In order to minimize potential bias and ensure a fair distribution of participants, we will randomly assign subjects from the outpatients and community cohort to either the intervention group or the control group in a 1:1 ratio. To prevent predictability, we will employ block randomization using variable block sizes [41]. This will involve generating randomization tables using Statistical Analysis System (SAS) software by our statistician. Cards will be prepared for the study, with allocation information concealed by a layer that matches the group sample size. Subjects will be recruited by our senior researchers in our project team, such as [name], [name], [name], [name], [name], [name], [name], and [name]. They will enroll participants and obtain signed informed consent from all eligible participants. Participants will select their card in a predetermined order. And based on the allocation information of the card, the senior researchers will divide them into the hearing aid intervention group or the healthy education group. Once chosen, the card will not be returned.

### Intervention

After randomization, every participant allocated to the hearing aid fitting group will get the binaural and behind-the-ear hearing aids, Widex-Evoke E-FA100 & E-FP50, with a full set of auxiliary accessories, purchased by Ninth People’s Hospital and distributed to each sub-center. Our professional audiologist will make adjustments for patients until they can hear what others say with a few noisy environmental sounds, which will make participants willing to learn the usage of hearing aids and wear them in their daily lives. In addition, some of the subjects with a long history of hearing loss may lead to poor effect of hearing aids. We will provide some suggestions on hearing rehabilitation for them, including reading newspapers out and talking to their families frequently. Patients are required to wear hearing aids for more than 10 h per day. The time of wearing hearing aids will be recorded by a system; thus, we can remind subjects. Furthermore, participants will maintain their hearing aids if needed and make regular adjustments to their hearing aids with the help of an audiologist.

The patients in the health education group will receive periodic health education from researchers as part of the study, including valuable guidance on hearing health, such as the importance of noise reduction, avoidance of ototoxic drugs, and development of healthy ear care habits.

Furthermore, we will make it clear to the participants that those who are allocated to the intervention group will benefit from using hearing aids free of charge for the rest of their lives, while those who are assigned to the control group will receive an extra allowance at the end of the trial period. Besides, in the hearing aids group, we will use the system in hearing aids to record the average duration of hearing aid use, and for those who do not meet the requirement, we will take measures such as the commissioning of hearing aids and online supervision. All participants will get subsidies for the cost of transportation for every follow-up visit.

In the follow-up stage, the patients of the two groups will be recalled to study centers to perform assessments of auditory tests and cognitive evaluations at 6, 12, and 24 months after the intervention. Researchers will contact those who are near the date of the follow-up visit and make an appointment with them in advance.

Subjects are not allowed to participate in another trial which may influence the results during the study.

### Outcome measurements and follow-ups

The assessment of the following outcomes will take place during the screening, baseline measurements, and follow-up visits at 6, 12, and 24 months after the intervention (refer to Table 1). Our researchers will conduct all measurements using the same standardized procedures.

**Table 1 Tab1:**
[figure not shown]
Outcomes and data collection in the study

“√(HA)” means that only participants in hearing aid fitting groups will perform the assessments, while “√” means both groups will perform them

#### Primary outcome measure

The primary outcome of the study is the rate of patients with ARHL and MCI progressing to dementia in two groups after different interventions.

#### Secondary outcome measures

##### General information

During the screening process, participants will be provided with a thorough understanding of our study and will be required to sign an informed consent form. Following this, our researchers will ask participants a series of questions regarding their educational background, hearing health, and whether they have used hearing aids within the past year. It is important to note that individuals with neurosyphilis or hypothyroidism will not meet the inclusion criteria, as these conditions may contribute to further cognitive decline in the patient [42, 43]. Once the screening is complete, eligible participants will be asked to complete a questionnaire specifically designed to collect basic information such as demographic characteristics, lifestyle factors, general health conditions, hearing-related symptoms, and any previous history of hearing disorders.

##### Audiological tests

Participants will undergo a series of audiological tests to evaluate the extent of their hearing loss. These tests will be conducted by audiologists from the hospitals at the study centers where participants have registered.

##### Pure tone audiometry

The main measurement is the pure tone audiometry. Our audiologists will evaluate the auditory threshold of the patients according to ISO 8253–1:2010 (en) [44] at a sound-treated booth. Patients will hear pure tones from small voice to loud at different frequencies through a headset. We intend to use the Astera (type1066) form NATUS, DNK, and Diagnostic Audiometer (AD229b) from INTERACOUSTICS, DNK to perform the audiogram as the evaluation results of the participants’ hearing level.

##### Tympanometry

Tympanometry is often used to assess the conditions of the middle ear, including the presence of fluid, changes in the internal structure, and the ear canal volume. It can be classified as type A, meaning the normal situation of the middle ear; type B, indicating that there is a significant abnormality in it; and type C, suggesting the negative pressure of the middle ear [45].

A listening test platform from INTERACOUSTICS A/S will be used to measure the tympanograms of both ears. Patients with type B will be ineligible for our study, which indicates the presence of fluid in the middle ear with the consequences of inflammation mainly, implying the secretory otitis media and potential conductive hearing loss [46].

##### Speech discrimination score (SDS)

Cognitive abilities, such as working memory and executive ability, play important roles in speech discrimination [47]. After the assessment of PTA, under the same initial environmental noise, the subjects will hear 10 monosyllables in the initial volume of their PTA + 20 dB HL at a sound-treated booth. We will record the percentage of correct monosyllables they retold as the SDS in the volume. By changing the signal-to-noise ratio (SNR), the maximum SDS among different SNRs will be confirmed when the participants’ SDS is up to 100% or the volume of monosyllables they heard reaches 90 dB HL. For the individuals, recovery will be considered if the maximum SDS increases by 10% or greater [48].

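### Speech discrimination 'recovery' is a gain of one word in ten, which chance often produces at mid-range scores; for PTA above 70 dB HL the test also starts above its own end level

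*Protocol article*

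**What the plan says.** All but the last of these statements come from the protocol article, section Speech discrimination score (SDS).

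- **List and start level:** "the subjects will hear 10 monosyllables in the initial volume of their PTA + 20 dB HL at a sound-treated booth".
- **Score:** "We will record the percentage of correct monosyllables they retold as the SDS in the volume".
- **Score compared over time:** a maximum over several conditions, since "the maximum SDS among different SNRs will be confirmed when the participants’ SDS is up to 100" per cent. The alternative end point is that "the volume of monosyllables they heard reaches 90 dB HL".
- **Individual rule:** "recovery will be considered if the maximum SDS increases by 10% or greater". The article supports it with a literature reference. It gives no error rate or retest figure for the rule.
- **Eligibility:** the Inclusion criteria section admits PTA ("pure tone average at 0.5, 1, 2, 4 kHz") from 35 to below 80 dB HL.

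The section speaks of changing the signal-to-noise ratio, yet one of its end points is a volume. The number of lists per visit therefore cannot be worked out from the text.

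**The concern.** A threshold for individual change should exceed what the test shows when nothing has changed. On a 10-word list the score moves in steps of 10 points, so a 10% rule counts every upward movement, however small, as recovery. Someone whose hearing and cognition are unchanged can meet it by repeating one more word correctly at follow-up. At stake is the meaning of the word recovery for a participant, and of any recovery percentage reported from it, especially within one group, where there is no comparator to show the chance rate.

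The level rule is a separate matter. The start level depends on PTA and the end level is fixed, so the two can cross inside the eligible range. The participants affected are those with the worst hearing.

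**Working it through.** **1. Threshold in words.** 10% of 10 words = 1 word. Reading 10% as a relative gain changes nothing: the smallest relative gain from a non-zero score is 9 to 10 words, which is 1/9 = 11%.

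**2. Chance of a one-word gain with no true change.** The article gives no figure to reproduce, so this is a model. Assumptions: each list is Binomial(10, p), lists and visits are independent, and p is the same at both visits. With k lists per visit at equal p, the maximum has probabilities m(x) = F(x)^k − F(x−1)^k, where F is the Binomial(10, p) distribution function. By symmetry

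P(gain of at least 1 word) = (1 − Σ m(x)²) / 2.

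Stopping early at 100% does not alter the maximum, so the formula still applies.

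Examples:
- p = 0.8, k = 1: Σ m² = 0.2238, giving (1 − 0.2238)/2 = 0.388.
- p = 0.8, k = 3: Σ m² = 0.3474, giving 0.326.
- p = 0.9, k = 3: Σ m² = 0.5906, giving 0.205.

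| True proportion correct | 1 list | best of 2 | best of 3 |
|---|---|---|---|
| 0.50 | 0.412 | 0.393 | 0.382 |
| 0.60 | 0.410 | 0.388 | 0.374 |
| 0.70 | 0.403 | 0.377 | 0.359 |
| 0.80 | 0.388 | 0.352 | 0.326 |
| 0.90 | 0.344 | 0.269 | 0.205 |
| 0.95 | 0.268 | 0.136 | 0.060 |

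The ranges are 33-41% for 50-80% correct, 20-34% at 90% and 6-27% at 95%.

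**3. Sensitivity.**
- *Unequal levels.* With two or three levels per visit, the others 10 to 30 points below the best, the result is 0.35-0.40 for a best-level p of 0.5-0.8, 0.29-0.32 at 0.9 and 0.20-0.24 at 0.95.
- *More lists.* With five lists at equal p it is 0.37 at 0.5, 0.34 at 0.7, 0.29 at 0.8, 0.10 at 0.9 and 0.01 at 0.95.

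**4. What the label separates.** Take one list per visit and a real rise in p from 0.7 to 0.8. P(Y > X), with X ~ Bin(10, 0.7) and Y ~ Bin(10, 0.8), is 0.604, against 0.403 with no change. About 60% would be labelled recovered, in a setting where about 40% would be labelled so anyway.

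**5. Size of the noise.** For one list the SD of the retest difference is 100·√(2p(1−p)/10): 22 points at p = 0.5 and 13 at p = 0.9. For the best of three lists, from m(x), it is 17 and 7 points. The single-list SD should not be applied to the maximum.

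**6. Levels.** Start = PTA + 20. PTA 35 gives 55 dB HL and PTA 70 gives 90. PTA between 70 and 80 gives more than 90 and up to just under 100. The start passes the 90 dB HL end level whenever PTA > 70, and such participants are eligible.

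**The case against.** Several counter-arguments have weight.

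- **Not a planned responder analysis.** The rule is offered for reading one person's score. The Statistical methods section compares groups by means with 95% confidence intervals and mentions mixed models. A reader might infer that the trial will compare recovery rates between arms and that this contrast would be diluted. The article states no such comparison. What stands is the unreliability of the individual label, and of a recovery percentage if one is reported.
- **The chance rate depends on the score.** A reader might infer that a third or more of all unchanged participants would be called recovered. That needs true scores away from the ceiling: for one list, between about 9% and 91%. The procedure seeks the best score, so many participants may sit near 100%, where the rate is much lower. More lists also lower it. Learning effects or retest correlation could move it either way.
- **PTA above 70 is workable.** One can read the rule as a single list at the start level, whose score becomes the maximum. So it goes too far to say that these participants have no SDS. But the text does not state this reading, and it would give them a maximum over one list while others have several.
- **Unseen sources.** The 10% rule cites a source not at hand, and a fuller protocol may give list counts and step sizes. Neither changes the arithmetic of a 10-word list, which the article itself fixes, or the crossing of the two stated levels.

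**Conclusion.** The point holds in a limited form. That the rule is one word in ten, and that the start level exceeds the end level for eligible PTA above 70 dB HL, follows directly from the text. The chance-recovery percentages are model results. They assume independent binomial scoring, no true change and one to three lists at equal difficulty, and they should be quoted with their range and the decline towards the ceiling. Even at the lower rates, a label met by the smallest recordable gain is a poor basis for saying that a person has recovered.

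A reader might take this as a threat to the trial's main conclusion. It is not: SDS is a secondary outcome, and neither the dementia outcome nor the sample size uses it. How many participants have PTA above 70 is not given, so the reach of the level conflict is unknown.

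**What to change.** 1. Do not report or interpret SDS recovery by the one-word rule.
2. Report the between-arm difference in SDS, adjusted for baseline SDS, with a method suited to a bounded maximum score, for example an ordinal model or a bootstrap interval. A plain binomial model suits only a single fixed list.
3. If an individual label is kept, set its cut-off from the retest variability of the maximum score, for the number of words and lists actually used. Summing the model's probabilities over gains of at least s words shows why this matters. For true scores of 50-90%, a false-recovery rate of 2.5% or less needs 4 to 5 words with one list but 2 to 4 words with the best of three. A single-list cut-off cannot be carried over.
4. Reconcile the PTA range in the Inclusion criteria with the start and end levels in the SDS section, and state how participants with PTA above 70 dB HL are tested and scored.

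The cost is outcome and analysis wording; no change to sample size or visits is needed. The downside is the loss of a simple recovered percentage. Item 3 also needs retest data or a stated model.

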### Statistical analysis

#### Sample size

To detect the clinically relevant difference in the dementia rate after the hearing aid fitting compared with the health education group, the sample size of this study is calculated as follows. Our pilot study results showed that 3 of 30 patients with ARHL and MCI wearing hearing aids developed dementia within a year. Literature reported that 18% of the elderly with MCI progressed to dementia every year [73]. In conclusion, by using PASS software (Vision 15), *α* was set at 0.05, 1 – *β* = 0.8, and hearing aid fitting and health education group were set at 1:1; thus, 292 cases in each group were calculated. Considering the 15% of drop-out rate, we designed 344 cases in each group, and a total of 688 cases. Shanghai Ninth People’s Hospital will be responsible for 516 cases, Shanghai Sixth People’s Hospital for 103 cases, and Shanghai Ruijin Hospital for 69 cases. Furthermore, Shanghai Mental Health Center will provide training about cognitive evaluations for our researchers and recommend eligible patients for our study.

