#### Statistical methods

The mean and standard deviations, or the median and quartiles, will be used to describe the baseline features of both the hearing aid fitting group and the health education group, depending on the normality of the data. The unpaired *t*-test will be used to calculate the differences between the control and intervention groups. For within-group comparisons, paired *t*-tests will be used for continuous measures. Non-parametric tests will be used to compare data that do not follow a normal distribution. The differences in outcomes between groups will be determined by calculating the means and 95% confidence intervals. A *P* value < 0.05 will be considered statistically significant. Additionally, mixed effects models, COX regression, and multifactorial linear regression will be utilized to further explore the association between hearing aid fittings and cognitive improvement.

Intention-to-treat analysis will be conducted on all subjects enrolled in the group. Additionally, a per-protocol analysis will be performed on subjects with high compliance, specifically those who have worn hearing aids for the duration required by the experiment. To handle missing data, multiple imputation will be utilized. Complete case analyses will be conducted as a sensitivity analysis. It is important to note that all analyses will be performed on an intention-to-treat basis.

We will perform an interim analysis when all subjects complete the 12-month follow-up visits using the baseline data and follow-up data collected at 6 and 12 months after the interventions, and if the results of the interim analysis are positive, we will consider terminating the study.

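### The speech discrimination recovery rule cannot be met by a participant already at 100% at baseline, and the entry criteria admit such participants

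*Protocol article*

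**What the plan says.** The section on the speech discrimination score (SDS) describes a short test: "the subjects will hear 10 monosyllables in the initial volume of their PTA + 20 dB HL". Conditions are then varied until the participant's "SDS is up to 100% or the volume of monosyllables they heard reaches 90 dB HL", and the best score is kept as the maximum SDS. A response definition for the individual participant follows: "recovery will be considered if the maximum SDS increases by 10% or greater". No provision is made for a maximum that is already 100% at baseline.

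The inclusion criteria require a pure tone average (PTA) from 35 to below 80 dB HL. Neither they nor the exclusion criteria limit baseline SDS.

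SDS is described under the secondary outcome measures, and the design section says: "Secondary outcomes, such as auditory and cognitive function evaluations, will also be measured in both groups". For comparisons between arms, Statistical methods names the unpaired t-test (non-parametric tests if the data are not normal) and adds: "The differences in outcomes between groups will be determined by calculating the means and 95% confidence intervals". Mixed and regression models are also named, but for exploring cognitive improvement. No analysis of a recovery proportion is described.

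**The concern.** A response definition should be attainable by every participant to whom it is applied. Here an eligible group cannot attain it. A participant who scores 100% at baseline and keeps 100% falls in the same class as one who stays at 40%. This is a flaw in a rule that the article states, so it goes beyond detail left to an analysis plan.

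What is at stake is how a recovery rate would be read. If participants at ceiling stay in the denominator, the rate in each arm is lower than among those who could improve, and the absolute difference between arms shrinks with it. The general plan for outcomes, an unadjusted comparison of means, also makes no use of the baseline SDS that would put each participant's follow-up score in context.

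**Working it through.** **Stated figures.** The article gives no figure for SDS recovery. Its only sample size is for dementia, 10% (3 of 30) against 18%. With unpooled variances, two-sided 0.05 (sidedness is assumed) and power 0.80: (1.960 + 0.842)² × (0.18 × 0.82 + 0.10 × 0.90) / 0.08² = 7.849 × 0.2376 / 0.0064 = 291.4, so 292 per arm. Then 292 / 0.85 = 343.5, so 344 per arm and 688 in total. This reproduces the plan, and nothing below alters it. The 292 is used below as the number evaluated per arm.

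**Step 1: who is shut out.** With 10 words the score moves in 10-point steps. From 90% to 100% is 10 points, or 10/90 = 11.1% in relative terms, so the rule can be met from 90% whether 10% is read as points or as relative change. Only a baseline maximum of exactly 100% is shut out.

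**Step 2: where the ceiling can arise.** Headroom from the starting level to the volume stop is 90 - (PTA + 20) = 70 - PTA.

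| PTA (dB HL) | Start (dB HL) | Headroom (dB) |
|---|---|---|
| 35 | 55 | 35 |
| 50 | 70 | 20 |
| 60 | 80 | 10 |
| 70 | 90 | 0 |

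From a PTA of 70 upwards the first presentation is already at or above the stop. Repeated attempts at 100% are therefore mainly open to participants with milder loss.

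**Step 3: is 100% at baseline plausible?** The documents give neither an SDS distribution nor a number of test levels. Assume independent words with probability p correct and the same p at every level. Then P(10 of 10) = p^10, and for the best of three runs it is 1 - (1 - p^10)³.

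| p | One run | Best of three |
|---|---|---|
| 0.80 | 11% | 29% |
| 0.90 | 35% | 72% |

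These figures show that perfect baseline scores can occur. They do not estimate c, because they apply one value of p and one number of runs to everybody.

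**Step 4: effect on a recovery proportion.** Let p1 and p0 be the recovery rates among those below 100% at baseline, and c the share at 100%, equal in expectation in both arms by randomisation. Over all participants the rates are p1(1 - c) and p0(1 - c). The risk difference is (p1 - p0)(1 - c), and the risk ratio stays p1/p0. With assumed rates of 40% and 30% and 292 per arm:

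| c | Rates, all participants | Difference (points) | Risk ratio | Odds ratio | Power, all | Power, ceiling left out |
|---|---|---|---|---|---|---|
| 0% | 40 vs 30% | 10 | 1.33 | 1.56 | 72% | 72% |
| 10% | 36 vs 27% | 9 | 1.33 | 1.52 | 65% | 67% |
| 20% | 32 vs 24% | 8 | 1.33 | 1.49 | 58% | 62% |
| 30% | 28 vs 21% | 7 | 1.33 | 1.46 | 50% | 56% |
| 50% | 20 vs 15% | 5 | 1.33 | 1.42 | 36% | 43% |

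Leaving out those at ceiling restores the 10-point difference. It regains only about 2 to 8 points of power, because the denominator falls to 292(1 - c).

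**The case against.** The strongest reply is that the article never describes the analysis that would do harm. The rule is worded for individuals, no denominator or comparison of recovery between arms is stated, and the methods name means with confidence intervals. Denominators can properly be left to an analysis plan. This stands: a reader might infer that participants at ceiling are counted as not recovered in a comparison of arms, but the documents do not say so. The loss in Step 4 is therefore conditional. What remains is that the rule, as stated, cannot be met by an eligible group.

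A reader might also infer that the ceiling shrinks any difference between arms, or makes the result reflect mildness of loss more than the intervention. Neither follows. The absolute difference is scaled, the risk ratio is not, a zero difference stays zero, and randomisation balances the ceiling share in expectation. A proportion over all participants is also a legitimate quantity if that is what is wanted.

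Nor does the text support the reading that testing drives everyone to 100%. The 90 dB HL stop is an equal alternative.

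Finally, the ceiling shares in Step 3 depend on the short list. Under the same model with 50 words, 0.90^50 = 0.5% (best of three 1.5%), against 35% and 72% with 10 words. Under that model the problem mostly disappears with a longer list. It would persist only for participants whose true score is close to 100%, and the documents do not say how many there are.

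**Conclusion.** The point holds as a limited one. A baseline maximum SDS of 100% makes recovery impossible under the stated rule, and nothing in the entry criteria excludes such participants. If a recovery proportion is taken over all participants, the rates and the absolute difference are multiplied by (1 - c): a 10-point difference becomes 9, 8 or 7 points at c = 10%, 20% or 30%. The risk ratio is unchanged and there is no bias between arms.

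The size cannot be settled from the documents, because c is not given and the 40% and 30% recovery rates are assumptions. SDS is secondary. The primary outcome, stated as "The primary outcome of the study is the rate of patients with ARHL and MCI progressing to dementia", and its sample size are unaffected.

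**What to change.** 1. Make the main SDS analysis a comparison of follow-up maximum SDS between arms, adjusted for baseline maximum SDS, in all participants. This replaces the unadjusted t-test for this outcome and uses a value already planned for collection. Follow-up scores are still capped at 100%, so the ceiling is handled better but does not vanish.
2. Report the recovery proportion among participants whose baseline maximum SDS is 90% or lower, and give the number at 100% in each arm beside it.
3. Confirm that this baseline SDS is measured before allocation, so that the subset is defined before randomisation. The timeline section lists random allocation ahead of baseline evaluation, so the order should be made explicit.

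The cost is wording and one adjusted model, best settled before the 12-month interim analysis. The recovery proportion will have a smaller denominator and gain little power. Selecting on a noisy baseline of 90% or lower will also raise apparent recovery in both arms through regression to the mean, so the proportion should be read as a comparison between arms and not as a rate in its own right.
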